**Outcomes**

Our key outcomes for this analysis will be the number of pro, con, or neutral articles. We will analyze whether the distribution of these key outcomes differs by time period, proposed cause of high SSB consumption and proposed solution.

**Statistical testing**

First, we will conduct a descriptive analysis of the articles obtained in our search according to whether they are for supporting the tax, against the taxed, or mixed (Table 5). Next, we will conduct proportions testing to test whether there are significant differences in the percentage of positive and negative articles in the time periods before versus after the South African SSB tax.

**Table 5. Framing of news documents covering the South African SSB tax before and after it was passed in April 2018**

| **Source** | **Pro (%)** | **Con (%)** | **Mixed (%)** |
| --- | --- | --- | --- |
| *Pre-tax period total* |  |  |  |
| Source 1 (n = X) |  |  |  |
| Source 2 (n = X) |  |  |  |
| *Post-tax period total* |  |  |  |
| Source 1 (n = X) |  |  |  |
| Source 2 (n = X) |  |  |  |

Next, we will measure the prevalence of different explanations for the cause of excessive SSB consumption and intake of added sugars, following the methods of Buckton and colleagues^62^ (Table 6). We will categorize articles into one of five broad categories: relating to the role of individual decision making for health, the role of industry, the role of society and cultural norms, the role of the government, and the role of scientists (Table 6). Next, we will examine whether these different explanations are associated with support for the tax. We will perform cross-tabulation chi-squared testing to determine whether the percentage of articles supporting the tax differs by the category of cause identified (Table 6).

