**Overall Analysis Plan**

The objectives of this aim are (1) to examine the affective attributes (percentage pro/con/neutral) of online newspaper articles writing about the South African SSB tax and whether these change from before to after the tax; (2) examine reasons given for excessive sugar consumption and obesity and whether these causes differ by whether the article is pro, con, or neutral toward the tax; and (3) to test whether pro and con framed articles differ in their proposed solutions to reducing SSB intake (e.g. better education as individual level solution versus taxes as government policy solutions). This analysis will help identify the arguments that are used by either support for or against the SSB tax, which will inform future policymaking.

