Our unit of analysis will be the article. We will develop a coding instrument adapted from previous media content analysis work^63^ to assess the presence or absence of supportive (pro) and opposing (con) frames in news coverage about the SSB tax. Pro frames support the policy and argue for either reducing SSB consumption or improving health. Con frames oppose the policy and argue that the SSB tax is regressive (harmful to the poor), harmful to business, or otherwise unfair to certain groups. Articles will be coded as pro, con, or neutral. Neutral articles are either entirely factual or contain both positive and negative frames in equal amounts (>40% of either). To achieve acceptable intercoder reliability, articles will be read by the lead coder and a random 20% subsample will be read and coded by a colleague to ensure intercoder reliability of article content. We will use Krippendorff’s α of 0.8 as a threshold for high agreement^103^.

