**Table 6. Frequency of mentioning potential drivers of high SSB consumption and excessive intake from added sugars**

| **Cause** | **n (%)** | **Pro (%)** | **Con (%)** | **Mixed (%)** |
| --- | --- | --- | --- | --- |
| ***Failure of the individual*** |  |  |  |  |
| Individual predisposition (biological, genetic, or psychological) |  |  |  |  |
| Personal choice |  |  |  |  |
| Family background |  |  |  |  |
| Parenting decisions |  |  |  |  |
| Individual dietary habits |  |  |  |  |
| ***Failure of Industry*** |  |  |  |  |
| Inadequate self-regulation of industry and lobbying |  |  |  |  |
| Production and sales of unhealthy products |  |  |  |  |
| Advertising and marketing |  |  |  |  |
| product pricing and pricing promotions |  |  |  |  |
| Insufficient healthy alternatives at restaurants |  |  |  |  |
| ***Failure of society*** |  |  |  |  |
| Geographic areas with few healthy options/abundant fast food |  |  |  |  |
| Entrenched tastes preferences for sweets |  |  |  |  |
| Schools do not provide sufficient nutrition education |  |  |  |  |
| ***Failure of government*** |  |  |  |  |
| Public health education is insufficient |  |  |  |  |
| Unhealthy food environment |  |  |  |  |
| Insufficient regulation or fiscal pressure on industry |  |  |  |  |
| Political behavior |  |  |  |  |
| ***Failure of science*** |  |  |  |  |
| Industry influence on nutrition research |  |  |  |  |
| Problematizing scientific consensus on link between sugar and poor health |  |  |  |  |

Finally, we are interested in whether the pro and con articles differ by the proposed solutions suggested in the articles (Table 7). We will perform cross-tabulation chi-squared testing to determine whether the percentage of articles supporting the tax differs by category of proposed solutions (Table 7).

**Table 7. Analysis plan testing whether there are significant differences between the number of pro and con articles for each proposed solution**

| **Proposed solutions** | **Pro *** | **Con*** |
| --- | --- | --- |
| Individual responsibility | ↓ | ↑ |
| Industry voluntary action | ↑ | ↓ |
| Societal responsibility and changing norms | ↑ | ↓ |
| Government regulation | ↑ | ↓ |
| Role of scientists | ↓ | ↑ |

*Pro and con indicate whether the article is either in favor or against the tax. Arrows indicate predictions for whether pro or con arguments will be more prevalent.

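### Aim 3 gives each article one of five cause categories, although Table 6 counts mentions of 19 drivers and one article can name several causes or none

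*Protocol*

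**What the plan says.** Under Aim 3, Sample Selection (Coding), the protocol states "Our unit of analysis will be the article". Articles are coded pro, con or neutral. The neutral group takes in purely factual articles as well as those that "contain both positive and negative frames in equal amounts".

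Under Statistical testing, between Tables 5 and 6, the plan is that "we will measure the prevalence of different explanations for the cause of excessive SSB consumption". The next sentence gives the coding rule: "We will categorize articles into one of five broad categories", namely individual, industry, society, government and science. Chi-squared cross-tabulation is then used to "determine whether the percentage of articles supporting the tax differs by the category of cause identified".

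Table 6 is titled "Frequency of mentioning potential drivers of high SSB consumption and excessive intake from added sugars". It has 19 driver rows under the five heads (5 individual, 5 industry, 3 society, 4 government, 2 science), each with a count and a pro/con/mixed split. It has no row for several causes or for no cause. The second objective in the Overall Analysis Plan is to "examine reasons given for excessive sugar consumption and obesity" and to see whether these causes differ by the article's stance.

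**The concern.** The rule and the table describe different variables. The rule gives one value per article from five exclusive options. The table is a multi-response count in which an article can appear in several rows or in none. The protocol gives no rule for picking a main cause and no code for several causes or for no cause.

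Both problem groups can be foreseen. Purely factual articles stay in the sample, and some may name no cause. Co-mention across heads is also plausible, because Table 6 places closely related drivers under different heads: weak self-regulation by industry and weak regulation of industry by government; nutrition education in schools (society) and public health education (government); areas with few healthy options (society) and an unhealthy food environment (government).

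What is at stake is the cause-by-stance association, which is the second objective of Aim 3. The Aim 3 introduction also asks whether articles that treat the problem as individual propose individual solutions, and that question uses the same cause variable.

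**Working it through.** The protocol gives no article count, mention rate, power or error rate for Aim 3, so there is no planned figure to reproduce. The check has two parts.

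**1. The text side by side.** The unit is the article, and the object of the coding sentence is articles. The stated purpose (prevalence of explanations), the objective (reasons, in the plural) and Table 6 (mentions) all allow several causes per article. The test uses one category of cause per article. These cannot all hold unless every article names causes under exactly one head.

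**2. An illustration under assumptions not in the protocol.** Five causes are mentioned independently. Half the articles are pro and half con; mixed articles are left out. Average mention rates for individual, industry, society, government and science are:
- low: 0.20, 0.20, 0.10, 0.15, 0.05
- middle: 0.40, 0.40, 0.20, 0.30, 0.10
- high: 0.60, 0.60, 0.40, 0.50, 0.20

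*Articles affected when mention does not depend on stance.* P(none) = product of (1 − p). P(exactly one) = P(none) × sum of p/(1 − p). P(several) is the remainder.
- low: none = 0.8 × 0.8 × 0.9 × 0.85 × 0.95 = 0.465; one = 0.465 × 0.840 = 0.391; several = 0.144
- middle: none = 0.6 × 0.6 × 0.8 × 0.7 × 0.9 = 0.181; one = 0.181 × 2.123 = 0.385; several = 0.433
- high: none = 0.4 × 0.4 × 0.6 × 0.5 × 0.8 = 0.038; one = 0.038 × 4.917 = 0.189; several = 0.773

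*Association put in.* Industry is named more in pro articles and individual causes more in con articles, each with odds ratio 3. The odds are multiplied by √3 in one stance and divided by √3 in the other. At the middle rate industry is named in 0.4√3/(0.6 + 0.4√3) = 0.536 of pro and (0.4/√3)/(0.6 + 0.4/√3) = 0.278 of con articles, a difference of 0.258.

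*Methods compared*, 3000 runs per setting:
- (a) one forced code, drawn at random from the causes mentioned, or from all five if none, with one 5×2 chi-squared test at 0.05
- (b) five present/absent indicators, each with a 2×2 test at 0.05/5 = 0.01
- (c) all mentions stacked in one 5×2 table

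| Mention rates | Pro − con difference for industry: (b) | (a) | Shrinkage | Power, N = 150: (b) | (a) | Power, N = 300: (b) | (a) |
|---|---|---|---|---|---|---|---|
| low | 0.178 | 0.153 | 14% | 79% | 52% | 99% | 85% |
| middle | 0.260 | 0.191 | 27% | 95% | 71% | 100% | 96% |
| high | 0.260 | 0.147 | 43% | 94% | 48% | 100% | 80% |

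Differences and shrinkage are from the N = 150 runs, with shrinkage = 1 − (a)/(b), e.g. 1 − 0.147/0.260 = 0.43. At N = 300 the largest is 1 − 0.145/0.258 = 0.44.

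*With no true association*, rejection at nominal 5% was 4.3–5.4% for (a), 4.2–5.4% for (b) and 0.1–2.8% for (c). Stacking counts the same article in several rows, so the cells are not independent and the test does not keep its nominal level. Here it was too conservative.

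**The case against.** The strongest reply is that one loose sentence is being held against its context. The paragraph speaks of explanations in the plural, Table 6 has a multi-response layout, and the five heads may only be a way of grouping the drivers. The protocol also follows a cited UK newspaper content analysis and says a coding instrument will be developed, where rules for several or no causes might be settled. This has some force, but the sentence sorts articles, and the test needs one category per article. The protocol states this rule itself, so the point is not a detail deferred to another document. If grouping was meant, the sentence still has to change.

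Other parts of the reply stand:
- A reader might infer that articles with several causes receive a wrong code. A single code for them is incomplete and arbitrary, not false.
- A reader might infer that articles naming no cause must be miscoded. They could simply fall outside a table of causes identified; the protocol does not say.
- A reader might infer that the association could be created by the coding. The simulation does not show that: forced coding without regard to stance kept false positives near 5%. A coder who lets stance guide the choice could bias it either way, but this was not modelled, and the protocol plans a 20% double-coded sample with a Krippendorff's alpha threshold of 0.8.
- A single pooled chi-squared test on mentions is one possible reading of Table 6. The protocol does not propose it.
- Pro and con frames concern the policy. That mixed articles are the ones naming several causes is not supported by the text.

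**Conclusion.** The single-category rule conflicts with the purpose stated in its own paragraph and with Table 6. Used as written, it discards co-mentioned causes by an undefined choice and leaves articles without a cause uncoded. The expected harm is attenuation and lost power on the second objective of Aim 3: in the illustration, 14–44% shrinkage, and power of 48–71% against 79–95% with 150 articles. If Table 6 is filled by mentions instead, its rows overlap and must not be pooled into one chi-squared table.

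The sizes rest on assumed mention rates, independence between causes, an odds ratio of 3, assumed article counts and a random choice of code. Part of the loss comes from giving no-cause articles a random code; leaving them out would change it, and that was not computed. The direction of the effect and the textual conflict are firm; the magnitude is not. This should be corrected before coding, because discarded mentions can be recovered only by re-reading the articles.

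**What to change.** Replace the sentence that puts articles into one of five categories. Code each of the five cause categories, and each Table 6 driver, as present or absent per article, with several or none allowed. Test each category against stance in its own table (present/absent by pro, con and mixed), and state how the five tests are handled for multiplicity; Bonferroni, for example, gives 0.05/5 = 0.01 per test. Say that Table 6 percentages need not add to 100. Code the Table 7 solutions the same way. Report intercoder agreement per cause category in the 20% double-coded sample where counts allow, since agreement will be unstable for rare causes.

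The cost is a slightly longer coding form and five tests at a somewhat stricter threshold instead of one. If a single category is preferred, a written main-cause rule with a code for no cause would remove the conflict but would still discard co-mentions.

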**Table 6. Frequency of mentioning potential drivers of high SSB consumption and excessive intake from added sugars**

| **Cause** | **n (%)** | **Pro (%)** | **Con (%)** | **Mixed (%)** |
| --- | --- | --- | --- | --- |
| ***Failure of the individual*** |  |  |  |  |
| Individual predisposition (biological, genetic, or psychological) |  |  |  |  |
| Personal choice |  |  |  |  |
| Family background |  |  |  |  |
| Parenting decisions |  |  |  |  |
| Individual dietary habits |  |  |  |  |
| ***Failure of Industry*** |  |  |  |  |
| Inadequate self-regulation of industry and lobbying |  |  |  |  |
| Production and sales of unhealthy products |  |  |  |  |
| Advertising and marketing |  |  |  |  |
| product pricing and pricing promotions |  |  |  |  |
| Insufficient healthy alternatives at restaurants |  |  |  |  |
| ***Failure of society*** |  |  |  |  |
| Geographic areas with few healthy options/abundant fast food |  |  |  |  |
| Entrenched tastes preferences for sweets |  |  |  |  |
| Schools do not provide sufficient nutrition education |  |  |  |  |
| ***Failure of government*** |  |  |  |  |
| Public health education is insufficient |  |  |  |  |
| Unhealthy food environment |  |  |  |  |
| Insufficient regulation or fiscal pressure on industry |  |  |  |  |
| Political behavior |  |  |  |  |
| ***Failure of science*** |  |  |  |  |
| Industry influence on nutrition research |  |  |  |  |
| Problematizing scientific consensus on link between sugar and poor health |  |  |  |  |

Finally, we are interested in whether the pro and con articles differ by the proposed solutions suggested in the articles (Table 7). We will perform cross-tabulation chi-squared testing to determine whether the percentage of articles supporting the tax differs by category of proposed solutions (Table 7).

**Table 7. Analysis plan testing whether there are significant differences between the number of pro and con articles for each proposed solution**

| **Proposed solutions** | **Pro *** | **Con*** |
| --- | --- | --- |
| Individual responsibility | ↓ | ↑ |
| Industry voluntary action | ↑ | ↓ |
| Societal responsibility and changing norms | ↑ | ↓ |
| Government regulation | ↑ | ↓ |
| Role of scientists | ↓ | ↑ |

*Pro and con indicate whether the article is either in favor or against the tax. Arrows indicate predictions for whether pro or con arguments will be more prevalent.

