**Expected Results**

We expect that coverage peaked in April 2018 after the passing of the SSB tax, with a significantly greater percentage of anti-tax articles published after the tax as a reaction against it. These negative articles will be more likely to question the role of sugary beverages and added sugars as contributors to weight gain and poor health outcomes. These con articles will be more likely to suggest preferred individual level solutions such as making better choices and exercising more instead of policy solutions, which will be suggested to be economically unjust (e.g. loss of jobs or targeting the poor).

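### Table 7's caption and footnote describe a pro-versus-con count within each solution, which is not the stance-by-solution association that the text and objective 3 set out to test

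*Protocol*

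**What the plan says.** All places are in Aim 3 of the protocol.

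- **Overall Analysis Plan, objective 3:** the purpose is "to test whether pro and con framed articles differ in their proposed solutions to reducing SSB intake".
- **Outcomes:** "We will analyze whether the distribution of these key outcomes differs by time period, proposed cause of high SSB consumption and proposed solution".
- **Statistical testing, sentence introducing Table 7:** cross-tabulation chi-squared testing is to determine "whether the percentage of articles supporting the tax differs by category of proposed solutions (Table 7").
- **Table 7 caption:** "Analysis plan testing whether there are significant differences between the number of pro and con articles for each proposed solution".
- **Table 7 footnote:** "Arrows indicate predictions for whether pro or con arguments will be more prevalent".

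Table 7 has five rows. It predicts con above pro for individual responsibility and for the role of scientists, and pro above con for industry voluntary action, societal responsibility and government regulation. It has columns for pro and con only.

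**The concern.** The first three statements describe association: does the mix of stances change from one solution to another? The caption and footnote describe a comparison inside each row: are there more pro or more con articles among those proposing this solution? These are different quantities. The count in a row depends on the stance-solution link and also on how much of the whole sample is pro or con. If coverage as a whole leans one way, most rows will lean that way even when stance and solution are unrelated.

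The mismatch matters because a single chi-squared test over the whole table cannot by itself confirm or refute five directional predictions. An analyst asked whether each arrow was right would turn to the caption and footnote. Arrows for the majority stance would then tend to look confirmed and the others refuted, whatever the answer to objective 3.

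**Working it through.** The protocol gives no article count, stance split or significance level for Aim 3, so there is no stated figure to reproduce. The numbers below are illustrations under stated assumptions: two-sided 0.05, pro and con articles only, one solution per article in steps 1 to 3, and solution shares of 25, 15, 15, 35 and 10%.

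**1. Same data, two readings, no association.** Take 200 articles, 140 pro and 60 con, split exactly 70:30 in every solution. The count comparison in a row is chi-squared = (pro − con)² / (pro + con), 1 df.

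| Row size | Pro | Con | Chi-squared | p |
|---|---|---|---|---|
| 50 | 35 | 15 | 20²/50 = 8.0 | 0.005 |
| 30 | 21 | 9 | 12²/30 = 4.8 | 0.028 |
| 30 | 21 | 9 | 12²/30 = 4.8 | 0.028 |
| 70 | 49 | 21 | 28²/70 = 11.2 | 0.0008 |
| 20 | 14 | 6 | 8²/20 = 3.2 | 0.074 |

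Four of five rows fall below 0.05. The 5×2 association test on the same table has every observed count equal to its expected count, so chi-squared = 0 on 4 df and p = 1.0.

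**2. How often a row would be significant with no association.** This is the binomial probability that the same 1-df test rejects equal counts when the true pro share in the row equals the overall share.

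| Overall pro share | Row of 20 | Row of 40 | Row of 100 |
|---|---|---|---|
| 60% | 13% | 21% | 54% |
| 70% | 42% | 70% | 99% |

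An exact two-sided binomial test in place of chi-squared gives 46% and 98% for rows of 100. The rate runs from modest to near certain, depending on row size and imbalance.

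**3. The test named in the text.** Simulating the 5×2 chi-squared test with stance independent of solution (10,000 samples per setting; 100, 200 and 400 articles; pro share 50, 60, 70 and 80%) gives rejection rates of 4.4% to 5.3%. The overall majority has no material effect on it.

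**4. The count rule can also reverse a true association.** Take 140 pro and 60 con articles, with individual responsibility proposed by 30 pro and 25 con.

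- Share of pro articles proposing it: 30/140 = 21%. Share of con articles: 25/60 = 42%.
- 2×2 chi-squared without continuity correction: 200 × (30×35 − 110×25)² / (140 × 60 × 55 × 145) = 200 × 1,700² / 66,990,000 = 8.63, p = 0.003. The direction is the one Table 7 predicts.
- The text's orientation agrees: 30/55 = 55% of articles proposing this solution are pro, against 140/200 = 70% overall.
- The count rule compares 30 with 25. Pro is more prevalent (exact binomial p = 0.59), so the con-up arrow would be judged wrong.

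**The case against.** The strongest reply is that the protocol names only one test for Table 7, the cross-tabulation chi-squared test, in the sentence directly above the table. Objective 3 and the outcomes statement point the same way. The caption and footnote name no test statistic and no null hypothesis of equal counts, and a count of articles is a natural loose label for a cross-tabulation. On this view the defect is one of labelling, and the rates in step 2 belong to a test that the protocol never prescribes.

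Most of that stands. A reader might infer that the Aim 3 test is invalid, or that a pro or con majority would by itself make the Table 7 results significant. The documents do not support either: the named test is unaffected by a majority, and even under the count reading small rows or mild majorities often stay non-significant.

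A reader might also infer five separate tests that need a multiplicity correction. The text calls for a cross-tabulation across solution categories, not five tests, and handling of any row-wise follow-up could sit in a statistical analysis plan that is not shown.

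Nor does the expectation of "with a significantly greater percentage of anti-tax articles published after the tax as a reaction against it" establish a lopsided sample. It predicts a shift over time and gives no overall split. It only means that a balanced sample should not be taken for granted.

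What the reply does not remove is that the caption presents itself as the plan for testing, and that the footnote is the only stated rule for reading the arrows. That rule answers a different question from objective 3.

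**Conclusion.** Wrong as written, minor in severity. The caption and footnote of Table 7 conflict with the chi-squared association test stated just above the table and with objective 3. Objective 3 and the text do not conflict with each other: solutions differing by stance and stance differing by solution are the same hypothesis under a chi-squared test of association.

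The consequence is conditional. If the caption and footnote are used to judge the row predictions, an overall majority could make rows significant with no stance-solution link, or could reverse the reading of a real one. Its size cannot be fixed from the protocol. Every count, share and significance level used in the illustrations is an assumption.

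**What to change.** Reword the Table 7 caption and footnote to match the text and objective 3. Each row should show the percentage of pro articles and the percentage of con articles that propose the solution, and the footnote should say that the arrows predict which percentage is higher. Keep the stated cross-tabulation chi-squared test as the test of association. No multiplicity procedure needs to be added on this account.

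The cost is an edit to one caption and one footnote. It needs no new data, coding or analysis, and there is no loss of power because the named test does not change.
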